## Abstract

**Background:**

Admission criteria that treat children with low mid-upper-arm circumference (MUAC), and low weight-for-height *z*-score (WHZ) are not aligned with the evidence on which children are at risk of mortality. An analysis of community-based cohort data from Senegal found that a combination of weight-for-age (WAZ) and MUAC criteria identified all children at risk of near-term death associated with severe anthropometric deficits. This study will address whether children with WAZ <−3 but MUAC ≥125 mm benefit from therapeutic feeding with ready-to-use therapeutic foods (RUTF) and whether a simplified protocol is non-inferior to the weight-based standard protocol.

**Methods:**

This is a prospective individually randomized controlled 3-arm trial conducted in the Nara health district in Mali. Children aged 6–59 months presenting with MUAC ≥125 mm and WAZ <−3 will be randomized to (1) control group receiving no treatment, (2) simplified treatment receiving 1 sachet of RUTF daily until WAZ ≥−3 for 2 visits, (3) standard treatment receiving RUTF according to WHZ category: (a) WHZ <−3 receive 200 kcal/kg/day until WHZ ≥−2 for 2 visits, (b) WHZ ≥−3 but <−2 receive 1 sachet daily until WHZ ≥−2 for 2 visits or (c) WHZ ≥−2 receive no treatment. All children will be followed up first fortnightly for 12 weeks and then monthly until 6 months post-enrolment. The primary endpoint will be measured at 2 months with the primary outcome being WAZ as a continuous measure. Other outcomes include other anthropometric measurements and a secondary endpoint will be observed at 6 months. A total of 1397 children will be recruited including 209 in the control and 594 in both the simplified and standard arms. The sample size should enable us to conclude on the superiority of the simplified treatment compared to no treatment and on the non-inferiority of the simplified treatment versus standard treatment with a margin of non-inferiority of 0.2 WAZ.

**Discussion:**

This trial aims to generate new evidence on the benefit of treating children with WAZ <−3 but MUAC ≥125 mm in order to guide the choice of admission criteria to malnutrition treatment and build evidence on the most efficient treatment protocol.

**Trial registration:**

This trial was registered at ClinicalTrials.gov: NCT05248516 on February 21, 2022.

**Supplementary Information:**

The online version contains supplementary material available at 10.1186/s13063-023-07890-0.

## Administrative information

Note: the numbers in curly brackets in this protocol refer to SPIRIT checklist item numbers. The order of the items has been modified to group similar items (see http://www.equator-network.org/reporting-guidelines/spirit-2013-statement-defining-standard-protocol-items-for-clinical-trials/). The SPIRIT check-list document can be found in supplementary information.

## Introduction

### Background and rationale {6a}

The field of nutrition divides undernutrition into two categories: micronutrient deficiencies and growth deficits. Micronutrient deficiencies arise when specific type 1 micronutrients, such as iron, are lacking in the diet [1]. These deficits give rise to a specific symptom, anemia in the case of iron, that is rather easy to identify [2] and treat via supplementation [3, 4]. Type 1 micronutrients include all vitamins as well as some minerals such as iodine, copper, and calcium [1]. Growth deficits occur when either type 2 micronutrients or macronutrients are lacking in the diet leading to slowed height and weight gain. Type 2 micronutrients include zinc, potassium, and magnesium [1].

Growth deficits are further divided into the overlapping subcategories of wasting, stunting, and underweight [5]. Being wasted is strictly defined as a weight-for-height *z*-score (WHZ) below −2, stunted as a height-for-age *z*-score (HAZ) below −2, and underweight as a weight-for-age *z*-score (WAZ) below −2 [6]. Both being stunted and wasted overlap heavily with the category of children who are underweight [5]. Up to 93% of underweight children are also stunted or wasted and 17% accumulate a degree of both deficits [5].

All growth deficits are associated with an increased risk of mortality compared to children with no growth deficits. Moderately (*z*-score between −2 and −3) stunted, underweight, and wasted children have a 2.3-, 2.6-, and 3.4-fold increased risk of mortality, respectively [7]. Severe (*z*-score below −3) stunting, underweight, and wasting are associated with 5.5, 11.6, and 9.4 increased risk of mortality, respectively [7]. Accumulating several deficits increases substantially the mortality risk: children with both stunting and wasting, either moderate or severe, have a 12.3-fold increase in their risk of mortality [8].

Currently, only severe wasting is intentionally addressed via therapeutic feeding [9–11]. Children are admitted to therapeutic feeding programs for severe acute malnutrition (SAM) if their WHZ is below −3, they have a mid-upper arm circumference (MUAC) below 115 mm or in the presence of edema [12]. MUAC is used to detect being wasted as it reflects muscle mass deficits [13, 14], predicts mortality [15], is quick and easy to measure, and thus is used in community screening campaigns to identify malnourished children [9].

However, it is unclear whether the use of WHZ <−3 and MUAC <115 mm is optimal for capturing all children at the highest risk of mortality and for targeting all that would benefit from nutritional supplementation. An analysis of community-based cohort data from Senegal found that up to 62% of children at risk of death associated with growth deficits were missed when using WHZ <−3 and MUAC <115 mm [16].

Nutritional treatment is currently prescribed based on the weight of the severely wasted child and aims to fulfill 100% of the daily nutrient needs of the recovering child [10, 11]. However, recent evidence has shown that it is possible to reduce the dose of ready-to-use therapeutic food (RUTF) prescribed without undermining the recovery of treated children [17, 18] all the while making treatment less costly per child [19].

Beyond reducing the RUTF dose prescribed, simplifying the dosing regimen to 1 or 2 daily sachets per child based on the MUAC category instead of weight has been proposed and tested with encouraging results [17, 18]. The advantage of such a simplified dosage is both its simplicity to health agents prescribing treatment as well as to caregivers administering the treatment to children at home.

The simplified dosing regimen is only one aspect of a broader current initiative to towards simplifying malnutrition treatment [20]. Despite some improvements in treatment coverage over the past decade, still an estimated 70% of children with SAM and even more with moderate acute malnutrition (MAM) are left untreated in the community [21]. This is mostly attributed to the inexistence of screening and treatment services [22] which are often seen as burdensome and complex to run [23]. Simplified approaches to the detection and treatment of malnutrition have been proposed as a solution to scale up treatment services and enhance continuity of care [24].

One commonly proposed simplification is the combination of treatment of moderately and severely wasted children under the same program to ensure a continuity of care for wasted children and also prevent deterioration into more severe forms. Currently, children with MAM are eligible for supplementary feeding which can be in the form of a nutritional supplement providing 500 kcal/day [22]. However, treatment is oftentimes not available [22]. Recent recommendations on MAM treatment have also created some confusion about whether MAM should always be treated [25] despite evidence that moderately wasted children benefit from supplementation [26].

Moreover, there is growing interest in breaking the separation between stunting and wasting [27] and thus expanding the focus from treatment to include secondary prevention of severe malnutrition [28]. Traditionally, stunting has been largely seen as a non-treatable condition and is typically addressed through preventive interventions [29]. However, evidence is emerging that previous wasting episodes may be driving the development of stunting [30] and that stunting pre-disposes to wasting [31]. Both conditions seem to share some common risk factors and potential mechanisms driving the increased risk of mortality [27]. Particularly in contexts where both stunting and wasting are prevalent, addressing both seems critical to sustainably decrease the associated mortality risk.

Another simplification is the use of only MUAC and edema to admit children to treatment [32–36]. This enables leaving out the more time-consuming and error-prone procedures of weight and height measurements and the complex interpretation of WHZ tables. Admitting children with a MUAC <125 mm or edema to malnutrition treatment programs has been proposed as a means to facilitate decentralization of treatment to the less trained community health worker force [32, 34, 35].

However, using only MUAC <125mm and edema still leaves out children who are at risk of mortality associated with other growth deficits [16]. In a Senegalese cohort study that followed children in time, 34% of deaths among children with some growth deficit were not detected with a MUAC <125 mm [16]. On the other hand, all of these would have been captured with the use of WAZ <−2.8 [16]. This finding has led to the suggestion that WAZ <−3 could be added as an independent admissions criterion for therapeutic feeding programs in addition to MUAC <125 mm. This would enable capturing all wasted, stunted, and underweight children with an increased risk of mortality due to their growth deficits.

Currently, there is little evidence to inform the debate about whether children with MUAC ≥125 mm and WAZ <−3 respond to treatment and, if so, what treatment protocol should be used. There are numerous studies identifying optimal treatment protocols for children with MUAC <125 mm [32, 34, 35]. These protocols reduce the RUTF dose progressively towards the end of the treatment. Clinical trials have demonstrated that these alternative dosing protocols are non-inferior to the standard dosing regimen that keeps a “full” RUTF dose until the end of treatment [33, 34, 37]. However, to our knowledge, there is no data about optimal therapeutic feeding protocols for children with MUAC ≥125 mm and WAZ <−3. Currently, children with WAZ <−3 but MUAC ≥125 mm do not receive any treatment in areas implementing simplified protocols with MUAC-only-based admissions.

This study will assess whether children with WAZ <−3 but MUAC ≥125 mm benefit from therapeutic feeding and whether a simplified protocol is at least as effective as the more complicated weight-based standard protocol for this population. The publication of this study protocol aims to improve transparency and share information to support the development of similar studies that seek to study the optimization of the diagnostic criteria for malnutrition treatment and the therapeutic dosing of RUTF.

### Objectives {7}

The primary objective of this study is to assess whether therapeutic feeding with a simplified protocol results in 1) superior nutritional outcomes compared to no therapeutic feeding and 2) non-inferior nutritional outcomes compared to the WHZ and weight-based dosing regimen currently used in CMAM treatment, 2 months after diagnosis among children aged 6–59 months with MUAC ≥125 mm and WAZ <−3.

The secondary objective of this study is to assess whether therapeutic feeding with a simplified protocol results in (1) sustainably superior nutritional outcomes compared to no therapeutic feeding and (2) sustainably non-inferior nutritional status compared to the WHZ and weight-based dosing regimen currently used in CMAM treatment, 6 months after diagnosis among children aged 6–59 months with MUAC ≥125 mm and WAZ <−3.

Additional objectives include assessing whether the simplified protocol results in fewer children presenting negative outcomes compared to no treatment and non-inferior treatment outcomes compared to standard treatment.

### Trial design {8}

The study is a parallel group individually randomized controlled trial with three study arms allocated unevenly to test both a superiority and a non-inferiority hypothesis: 209 children will be recruited for the control arm (only involved in the superiority hypothesis testing) and 594 children in each intervention group.

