### Sample size {14}

Based on previous work on a similar population and similar intervention [48] we assumed a similar response to treatment and a similar SD for WAZ. Thus, for looking at hypothesis 1, we set an objective of measuring a meaningful impact of the simplified treatment (compared to no treatment) at a difference of 0.4 *z*-scores in WAZ. For calculating the sample size, we applied (a) SD of 1.1 WAZ, (b) power of 80%, (c) probability of type 1 error of 2.5%, and (d) obtained a sample size of 146 per group. Accounting for not having measures for 30% of children (particularly in the control arm) at 2 months due to (a) defaulting, lost-to-follow-up, or death (10%) or (b) development of MUAC <125 mm or edema (20%), we estimated needing 209 children in both control and simplified treatment arms each.

For looking at hypothesis 2 we set an objective of measuring a meaningful non-inferiority margin of 0.2 *z*-scores in WAZ. For calculating the sample size, we applied (1) SD of 1.1 WAZ, (2) non-inferiority margin of 0.2, (3) power of 80%, and (4) probability of type 1 error of 2.5% and obtained a sample size of 475 per group. Accounting for not having measures for 20% of children at 2 months due to (a) defaulting, lost-to-follow-up, or death (10%) or (b) development of MUAC <125 mm or edema (10%), we need 594 children in simplified and standard treatment arms each.

To be able to explore both hypotheses, we need 209 children in the control arm and 594 children in both the simplified and standard treatment arms meaning a total of 1397 children.

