## Discussion

This individually randomized controlled 3-arm trial evaluates the response to treatment of children with WAZ <−3 but MUAC ≥125 mm when treated with a simplified protocol versus standard protocol versus no treatment. If the results show that treatment is superior to no-treatment then this speaks for adding WAZ as an additional and independent admission criteria to MUAC <125 mm to treatment. If this study shows that the simplified treatment is non-inferior to standard treatment, then this contributes to the growing evidence base that the simplified protocol is as effective as the standard protocol in correcting childhood malnutrition.

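### Non-inferiority to standard is read as evidence of effectiveness without requiring that simplified treatment first beats no treatment, although the untreated arm needed for that is in the trial

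*Protocol article*

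**What the plan says.** Trial design {8} gives each arm its role: "209 children will be recruited for the control arm (only involved in the superiority hypothesis testing) and 594 children in each intervention group". Sample size {14} sizes the two hypotheses separately. Hypothesis 1 (simplified against no treatment) aims at "measuring a meaningful impact of the simplified treatment (compared to no treatment) at a difference of 0.4" WAZ. For hypothesis 2 (simplified against standard), "we set an objective of measuring a meaningful non-inferiority margin of 0.2" WAZ, and the authors "obtained a sample size of 475 per group". Both calculations use an SD of 1.1, 80% power and a "probability of type 1 error of 2.5"%, with no sidedness given.

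The Discussion attaches a separate conclusion to each result. On the second it says: "If this study shows that the simplified treatment is non-inferior to standard treatment, then this contributes to the growing evidence base", and continues that this evidence is for simplified being as effective as standard in correcting malnutrition. No condition on hypothesis 1 is attached.

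Three other places bear on this:
- Background and rationale {6a} says there is little evidence on whether these children respond to treatment.
- Intervention description {11a} and Table 1 give no RUTF to standard-arm children with WHZ ≥−2.
- Explanation for the choice of comparators {6b} says the control arm is there to show whether simplified, or any, treatment works.

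**The concern.** Non-inferiority shows only that simplified is not much worse than standard. It says something about effectiveness only if standard itself works in these children. In many trials this has to be borrowed from history. Here the article says there is little history to borrow, and an unknown part of the comparator is managed exactly like the control arm.

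The trial has a concurrent untreated arm that can settle the matter directly, but Trial design {8} keeps it out of the non-inferiority question and the Discussion does not bring it back. If neither regimen did anything, hypothesis 2 could still be met and reported as support for the simplified protocol.

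The 6-month endpoint is more exposed. Treatment lasts at most 12 weeks and follow-up runs to 24, so the arms may have drawn together by then, which makes non-inferiority easier to meet.

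**Working it through.** **1. Inputs, all from Sample size {14}.** SD 1.1; margin 0.2; superiority difference 0.4; evaluable 475 per arm for non-inferiority and 146 per group for superiority; losses of 20% and 30%.

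**2. The plan's own figures reproduce.**
- Non-inferiority: n = 2 × 1.1² × (1.960 + 0.842)² / 0.2² = 474.9, so 475 per arm (one-sided 2.5%, true difference 0). 475 / 0.8 = 593.75, so 594.
- Superiority: the normal formula at two-sided 2.5% gives 144, and the t-based calculation gives 146. One-sided 2.5% would give 119. 146 / 0.7 = 208.6, so 209.
- Total: 209 + 2 × 594 = 1397.

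The arithmetic is sound. Because sidedness is not stated, superiority results below are given for one-sided 2.5% and then two-sided 2.5%.

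**3. Chance of declaring non-inferiority when no treatment works.**
- Standard error, simplified minus standard: 1.1 × √(2/475) = 0.0714.
- Non-inferiority is declared if the observed difference exceeds −0.2 + 1.960 × 0.0714 = −0.0601.
- All three means equal: Φ(0.0601 / 0.0714) = Φ(0.842) = 80%.
- Simplified 0.1 WAZ worse than both standard and no treatment: Φ((−0.1 + 0.0601) / 0.0714) = Φ(−0.559) = 29%.

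The first figure is the planned 80% power. That power depends only on simplified equalling standard, not on either of them working.

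**4. Joint results.** Simulation of three normal arm means, 2,000,000 draws, evaluable 146/475/475, SD 1.1. The standard error for either treatment against control is 1.1 × √(1/146 + 1/475) = 0.104.

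| True gain over control (simplified, standard) | Non-inferiority declared | Declared, superiority failed | Declared, superiority met |
|---|---|---|---|
| 0, 0 | 80% | 77.6% / 78.8% | 2.4% / 1.2% |
| 0.4, 0.4 | 80% | 1.6% / 3.1% | 78.4% / 77% |

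With the superiority test placed first, the misleading claim falls from 80% to 1–2%. When both treatments gain 0.4, the legitimate claim falls from 80% to 77–78%.

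**5. The margin against the effect of standard.** The only effect stated is 0.4, for simplified against no treatment; 0.2 is half of it. The effect of standard is not stated. As an assumption, let each fed child gain 0.4, each unfed child 0, and let p be the unfed share of the standard arm, which the article does not give. Standard's average gain is then 0.4 × (1 − p).

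| p (assumed) | Gain of standard | 0.2 as share of it |
|---|---|---|
| 30% | 0.28 | 71% |
| 40% | 0.24 | 83% |
| 50% | 0.20 | 100% |
| 60% | 0.16 | 125% |

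**The case against.** **The two hypotheses already belong together.** Objectives {7} joins superiority and non-inferiority with an and in one primary objective, the comparators section gives the control arm the right purpose, and Outcomes {12} reports all three arms at both endpoints. A failed superiority test would therefore be visible beside the non-inferiority result. This is fair, and it lowers the risk of a reader being misled. But none of these passages makes one result a condition for the other, and Trial design {8}, Sample size {14} and the Discussion treat them separately.

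**Testing order can sit in the analysis plan.** Silence on the order would be no finding. Here the article states a role for the control arm and an interpretation of the result, and any gate written elsewhere would have to correct both.

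**Two stronger readings are tempting and do not hold.**
- A reader might infer that 0.2 exceeds the whole effect of standard, so that no treatment would itself pass. The unfed share is not given, and equal gain per fed child is an assumption, since children with WHZ <−3 get a weight-based amount under standard. Even at p = 50%, the true difference would lie on the margin, where the test passes only 2.5% of the time. In that model simplified feeds everyone and beats standard by 0.12 to 0.24 WAZ for p from 30% to 60%, so it does not describe the feared case of three equal arms.
- A reader might infer that non-inferiority should be claimed only if standard beats control. In the same model, that second gate would cut the chance of the claim from 94–97% with the superiority gate alone to 67–76% at p = 30% and 24–34% at p = 60%, although simplified is truly better than both. It would block a sound claim because the comparator is weak.

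**Conclusion.** The point holds as one of decision rule and interpretation, and the sponsor should act on it. As written, hypothesis 2 can be met and read favourably when no arm differs from no treatment: 80% of the time if all three means are equal, and about 78% of the time with superiority not shown. These figures rest on the article's SD and evaluable numbers and on normal arm means, without covariate adjustment or imputation.

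The sample size is not in error. If both hypotheses are met, simplified has been shown to work and the concern falls away. The harm is confined to non-inferiority met with superiority failed. The article does not show that the 0.2 margin is too wide for the effect of standard. It shows only that the margin is half of the one effect stated, with its share of standard's effect left open.

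**What to change.** 1. State a fixed order. Simplified against control is tested first; non-inferiority to standard is interpreted as evidence of effectiveness only if that test succeeds. Apply the same order at 6 months, and word the Discussion's conclusion on non-inferiority accordingly.
2. In Trial design {8}, remove the parenthesis that limits the control arm to superiority testing.
3. Prespecify the standard-control difference with its confidence interval, from the same model, and report it beside the non-inferiority result as supporting information, not as a condition for the claim.

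Cost: no extra children, one further contrast from the planned model and a few words of text. If both treatments gain 0.4, the chance of the non-inferiority claim falls from 80% to about 77–78%. If both gain only 0.2, it falls further, to 43% (one-sided 2.5%) or 33% (two-sided 2.5%), because superiority over control is then hard to show with 146 evaluable controls. The supporting contrast has 94.5–97% power if standard gains 0.4 but only 37–48% if it gains 0.2, a further reason not to make it a gate.

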## Methods: participants, interventions, and outcomes

### Study setting {9}

The study will be conducted in 11 health centers in the Nara health district of the Koulikoro region in Southern Mali. The district has a surface of 30,000 km^2^ and a population estimated at 351,517 inhabitants in 2021 of which 20% are children below 5 years of age [38]. The region is predominantly arid land [39] and the population is subsisting on small-scale farming and herding [40]. The region is less affected by insecurity and conflict compared to the North and Center regions. Food security in the region has been relatively stable since 2018 and categorized as minimally insecure or stressed [41–44]. However, access to health care remains an issue with 29% of the population in the district living over 15 km away from basic services [45]. In the region, only 48% of children 12–24 months of age have been fully vaccinated and malaria prevalence is 22% among children under 5 years of age [46]. Acute malnutrition prevalence as measured by a WHZ <−2 was estimated at 10.9% in 2021 [47]. IRC has been present in the area since 2015 supporting the nutrition activities including strengthening community screening activities and health care staff skills in managing acutely malnourished children. At the start of 2022, the district counted 39 public health centers providing outpatient care and one inpatient facility. The criteria used to select the study sites out of the 39 existing health centers were related to accessibility for study teams (no acute security threat) and for study population (access maintained between villages and health center during rainy season), and sufficient population size covered by health center to enable a constant enrolment rate of participants. The list of the study sites can be found at the trial registration page at ClinicalTrials.gov: NCT05248516.

Since 2018, the district has been implementing a simplified protocol to treat acute malnutrition [32] admitting children based on their MUAC measure (<125 mm) or presence of bilateral edema and discharging children after 2 consecutive measures of MUAC ≥125 mm. The prevalence of MUAC <125 mm in children 6–59 months of age is estimated at 2.6% in the Koulikoro region according to the latest national nutrition survey in 2021 [47]. Based on the same data, the proportion of children with MUAC ≥125 mm but with WAZ <−3 is estimated at 2.7%.

